### Sample Size

Consistent with the idea that this is a pilot study, with no established effect size data available to aid in power and sample size calculations, the research will use data that can be elicited from participants who can be enrolled within existing operational resources. This method is acceptable for pilot studies involving novel interventions and has been described by Haynes et al [70] as using “the participants I can get.” Therefore, the study will be limited to a sample size of 100, with about 50 participants recruited into each arm of the study. Patients with TRD are vulnerable to severe depressive attacks, and it can reasonably be expected that only a small number of eligible participants will enroll in and complete the study.

## Results

We hypothesize that participants enrolled in the rTMS plus iCBT treatment arm of the study will achieve superior outcomes compared with participants enrolled in the rTMS alone arm of the study on each outcome measure used.

### Outcomes

Outcome measures and time points are detailed in Table 2 and follow from the aim and objectives of the study. All measures (except patient experience questionnaire, interviews, and data extraction) are objective measures with published information regarding reliability and validity. The Hamilton Depression Rating Scale (HAM-D) [71,72] will be the primary outcome and all other measures will be secondary outcomes. These measures include the following: Columbia Suicide Severity Rating Scale (CSSRS) [73,74], Young Mania Rating Scale (YMRS) [75], Quick Inventory of Depressive Symptomatology Self Report-16 (QIDS SR-16) [76], Frequency, Intensity, and Burden of Side Effects Ratings (FIBSER; edited for rTMS) [77], Patient Rated Inventory of Side Effects (PRISE) [78], EuroQoL 5-Dimension 5-Level (EQ-5D-5L) [79,80], and World Health Organization Disability Assessment 2.0 (WHODAS 2.0) [81]. The primary outcome measure will be the mean change in the scores on the Hamilton Depression Rating Scale. Patient service utilization data and clinician-rated measures will also be used to gauge patient progress. Patient data will be analyzed with descriptive statistics, repeated measures, and correlational analyses. All quantitative data will be analyzed using SPSS (Version 26; IBM Corp) [82].

**Table 2 table2:** Client-oriented outcome measures.

Outcome measures				Time points assessed			
Variable type and construct		Tool	Rater	Baseline	1 month	3 months	6 months
**Symptom variables**							
	Depression	Hamilton Depression Rating Scale (HAM-D)	Clinician	✓	✓	✓	✓
	Depression	Quick Inventory of Depressive Symptomatology Self Report-16 (QIDS SR-16)	Client	✓	✓	✓	✓
	Suicidal ideation	Columbia Suicide Severity Rating Scale (CSSRS)	Clinician	✓	✓	✓	✓
	Mania	Young Mania Rating Scale (YMRS)	Clinician	✓	✓	✓	✓
**Functional variables**							
	Side effects	Frequency, Intensity, and Burden of Side Effects Ratings (FIBSER; edited for rTMS)	Client	✓	✓	✓	✓
	Side effects	Patient Rated Inventory of Side Effects (PRISE)	Client	✓	✓	✓	✓
	Disability measures	World Health Organization Disability Assessment 2.0 (WHODAS 2.0)	Client	✓	✓	✓	✓
	Quality of life	EuroQoL 5-Dimension 5-Level (EQ-5D-5L)	Client	✓	✓	✓	✓

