**Methods:**

This study is a prospective, two-arm randomized controlled trial. In total, 100 participants diagnosed with resistant depression at a psychiatric care clinic in Edmonton, Alberta, Canada, will be randomized to one of two conditions: (1) enrolment in rTMS sessions alone and (2) enrolment in the rTMS sessions plus iCBT. Participants in each group will complete evaluation measures (eg, recovery, general symptomatology, and functional outcomes) at baseline, 1 month, 3 months, and 6 months. The primary outcome measure will be the mean change to scores on the Hamilton Depression Rating Scale. Patient service utilization data and clinician-rated measures will also be used to gauge patient progress. Patient data will be analyzed with descriptive statistics, repeated measures, and correlational analyses.

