### Repetitive Transcranial Magnetic Stimulation

rTMS uses powerful (1.0-2.5 Tesla) focused magnetic field pulses to induce electrical currents in neural tissue noninvasively via an inductor coil placed against the scalp. Therapeutic rTMS is usually delivered by a trained technician or nurse under physician supervision. Unlike electroconvulsive therapy (ECT), no anesthesia is required. The therapeutic mechanism of rTMS is still under investigation, with mechanisms proposed at molecular, cellular, and network levels [37]. Standard protocols deliver rTMS once daily, 5 days/week. Stimulation 3 times/week has been reported as similarly effective, albeit with slower improvement and a similar number of sessions required overall [38]. “Accelerated” protocols with multiple daily sessions (2-10/day) are being explored to complete the course more rapidly [39,40]. Repeated rTMS sessions can exert therapeutic effects lasting several months [33]. Clinical trials and naturalistic studies have found maximal effects at 26-28 sessions [41,42]. Clinical experience concurs in suggesting 20 sessions before declaring treatment failure, with extension to 25-30 sessions if improvements occur [33].

More than 30 systematic reviews and meta-analyses have been conducted on rTMS in depression, with most studies involving participants with some degree of treatment resistance (ie, having failed at least 1 or 2 antidepressant trials). Overall, rTMS is considered a first-line treatment for MDD for participants who have failed at least 1 antidepressant treatment. Both high-frequency (10 Hz) rTMS of the left dorsolateral prefrontal cortex (DLPFC) and low-frequency (1 Hz) rTMS of the right DLPFC have demonstrated efficacy in numerous meta-analyses [43-46], with no differences in outcomes between them [43]. Hence both high-frequency left DLPFC and low-frequency right DLPFC are first-line rTMS protocol recommendations.

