## Methods

### Ethics and Dissemination

The study will be conducted per the Declaration of Helsinki (Hong Kong Amendment) and the Canadian guidelines for Good Clinical Practice. All participants will provide informed consent before study inclusion. The results will be disseminated at several levels, including participants, practitioners, academics/researchers, and health care organizations.

The study will be a prospective, parallel design, two-arm, rater-blinded randomized controlled pilot trial with a recruitment period of 12 months. It will involve active treatment for six weeks and an observation period of 6 months for each participant. An overview of the timeline for the project is in Table 1. The research will be carried out in an Addiction and Mental Health clinic in a large, sociodemographically diverse city in Western Canada (Edmonton, Alberta).

**Table 1 table1:** Gantt chart timeline.

Milestones		Year 1							Year 2			
		Q1	Q2		Q3		Q4		Q1		Q2	

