**Milestone 2: The recruitment of study participants**												
	2.1. Recruitment, baseline assessment, and randomization			✓		✓						
	2.2. Assignment into one of the two arms of the study			✓		✓						
	2.3. Delivery of iCBT and rTMS to participants			✓		✓		✓				

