The rTMS-trained health care practitioners’ team will determine a participant’s eligibility for the rTMS treatments. Once the individual has been accepted into the rTMS program, a member of our research team will introduce the study to him/her, give them a copy of the information leaflet, and ask if they would also be interested in enrolling in our study. The recruitment and an informed consent process will involve a face-to-face meeting with the eligible participant during the week of their rTMS eligibility assessment, which occurs 1 week before beginning the rTMS sessions. Participants can also withdraw from the study at any time without providing a reason. To withdraw, participants can contact the research coordinator to let him/her know. If participants leave the study, we will not collect new health information about them, and they may ask the research coordinator to withdraw any data we have already collected from them before data analysis and dissemination.

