### Interventions

Participants would be randomly assigned to receive either rTMS alone or rTMS plus iCBT. Participants in both arms of the study will attend an introductory visit to introduce the rTMS system to them and explain the procedure that will be carried out in each visit. Participants will be asked to complete standard questionnaires as part of their participation in the rTMS program. A week before the start of rTMS sessions, the participants will be invited into the clinic for motor threshold (MT) assessments, which are important for selection of stimulation intensities for each patient, and assessment for inclusion in the study. MT is roughly a measure of the TMS intensity necessary to evoke a peripheral motor response. These assessments will be done by the rTMS team, which includes health care practitioners trained on how to assess and use rTMS. Each of the assessments will take 3-5 minutes, and the total time will be 35-45 minutes. The timeline for visits will be the same for all participants. All participants will be scheduled to receive 30 sessions of rTMS treatments over 6 weeks as predetermined by Alberta Health Services' Strategic Clinical Network for Addiction and Mental Health. In addition, participants in the rTMS plus iCBT arm of the study will be assisted in registering for the iCBT program (MoodGYM) to receive unique login information. They will be assisted in participating in 12 one-hour sessions of iCBT at the clinic followed by rTMS treatments on the same day. These in-clinic iCBT sessions will be scheduled at about three-day intervals (ideally Tuesdays and Thursdays) so that participants receive two iCBT sessions each week. These in-clinic iCBT sessions are necessary to avoid poor treatment adherence and high discontinuation rates, as conducting these sessions by themselves at home may represent a major challenge for patients with TRD. Participants would also be encouraged to continue with iCBT treatments on their own at home, outside the sessions delivered in the clinic. The personal information relating to the MoodGYM website that will be collected consists of age group, gender, email address, password, answers to secret questions nominated, and the information the participants submit when using the MoodGYM website (including quizzes, workbooks, and diaries). In addition, the following information about participants’ usage of the MoodGYM website will be collected by using transient cookies: participants’ browser’s internet address, the date and time the site was visited, the pages that were accessed and the documents that were downloaded, the type of browser used, the number of bookmarks created, the last viewed date, the time of visit, and details about participant’s subscription excluding credit card details. MoodGYM has its own privacy policy that controls the personal information obtained from all participants under their respective User Data profile. There is no risk that a participant’s diagnosis could be exposed to the public should a breach at MoodGYM occur.

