### Follow-up Assessment

At 1, 3, and 6 months, a blinded researcher will contact all study participants and help them complete a range of assessment tools relating to the primary and secondary outcome measures. They will be offered the opportunity to complete the assessments face-to-face or over the phone. Qualitative data collection will be in the form of a patient experience questionnaire and a focus group workshop, which will be conducted at 3 and 6 months. At 6 months, data related to each person’s clinic/program attendance rates and utilization of health services will be compiled from administrative records by the blinded researcher.

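### At most one of the four FIBSER and PRISE ratings falls within the 6-week treatment course and none at its end, so tolerability during treatment is sampled only sparsely

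*Protocol article*

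**What the plan says.** Table 2 (Outcomes) lists two client-rated side-effect scales, the PRISE and the "Frequency, Intensity, and Burden of Side Effects Ratings (FIBSER; edited for rTMS"), both ticked at all four time points. The Outcomes section makes every measure other than the HAM-D a secondary outcome and names repeated measures among the analyses. The abstract gives the assessment times as "at baseline, 1 month, 3 months, and 6 months", and Follow-up Assessment says: "At 1, 3, and 6 months, a blinded researcher will contact all study participants". Neither says from what event the months are counted.

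On exposure, Interventions states: "All participants will be scheduled to receive 30 sessions of rTMS treatments over 6 weeks". The rTMS-plus-iCBT arm also has 12 one-hour iCBT sessions in the clinic, two a week, before rTMS on the same day. The design paragraph under Methods says: "It will involve active treatment for six weeks and an observation period of 6 months for each participant". It leaves open whether the 6 months contain the 6 weeks or follow them.

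The recruitment paragraph under Exclusion Criteria places consent in the week of the rTMS eligibility assessment, "which occurs 1 week before beginning the rTMS sessions". Table 1 groups "Recruitment, baseline assessment, and randomization" as one step. The same recruitment paragraph says that no new health information is collected from anyone who leaves the study. The opening of Results expects the combined arm to do better on every outcome measure, which takes in these two scales.

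**The concern.** A schedule suited to depression scores over six months has been applied unchanged to scales meant to record the side effects of a 6-week treatment. The scheduled treatment of the two arms differs in the 12 in-clinic iCBT hours. A tolerability difference caused by that added load should arise mainly while it is being delivered, and that is when the schedule has the fewest ratings.

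Three things are at stake. First, the between-arm comparison of tolerability during treatment rests on one rating at best. Second, participants who leave the study before month 1, possibly because they tolerate treatment poorly, give no on-treatment rating, so the rating that remains may favour those who coped. Third, Objectives says that the pilot is to supply effect sizes for a full trial. An estimate averaged over mostly off-treatment visits would carry a diluted tolerability effect forward.

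**Working it through.** **Inputs**
- Course: 30 sessions over 6 weeks, or 42 days (Interventions).
- Session frequency: "Standard protocols deliver rTMS once daily, 5 days/week" (Repetitive Transcranial Magnetic Stimulation section). The article states this for standard protocols; it is assumed to apply here.
- Ratings: baseline, 1, 3 and 6 months (Table 2).
- Baseline: about 1 week before the first session (recruitment paragraph and Table 1 together).
- One month = 365.25 / 12 = 30.4 days.

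**The plan's own figure.** 5 sessions a week × 6 weeks = 30, which matches. For iCBT, 2 a week × 6 weeks = 12, which also matches.

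**Placing the ratings.** With day 0 as the first session, a rating at month m falls on day (origin + 30.4 × m). It is on treatment if that day lies between 0 and 42. Otherwise the gap after rTMS is (day − 42) / 7 weeks. Since the article does not state the origin, all three plausible ones are shown.

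| Months counted from | 1 month | 3 months | 6 months | Ratings on treatment |
|---|---|---|---|---|
| First session (origin 0) | day 30.4, week 4.3, on treatment | day 91.3, 7.0 weeks after | day 182.6, 20.1 weeks after | 1 of 4 |
| Baseline (origin −7) | day 23.4, week 3.3, on treatment | day 84.3, 6.0 weeks after | day 175.6, 19.1 weeks after | 1 of 4 |
| End of treatment (origin 42) | day 72.4, 4.3 weeks after | day 133.3, 13.0 weeks after | day 224.6, 26.1 weeks after | 0 of 4 |

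The baseline rating precedes the first session under every origin.

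**Sessions received by the 1-month rating.** Counted from the first session: 4 full weeks × 5 = 20, plus up to 2 more, so about 20 to 22 of 30. Counted from baseline: 3 full weeks × 5 = 15, plus up to 2, so about 15 to 17. The last 8 (30 − 22) to 15 (30 − 15) sessions therefore follow the only on-treatment rating.

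**Weight in a summary over visits (illustration).** Suppose the arms differ by d at the 1-month visit and not at all at the others. An equally weighted mean over four visits shows d / 4, or 25% of d. Over the three post-baseline visits it shows d / 3, or 33%. The article does not say that such an average will be used; this shows what would follow if it were.

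**The case against.** The strongest reply is that the trial does have an on-treatment rating. Under the two origins closest to the text, the 1-month rating comes after half to about three quarters of the sessions and allows a randomized comparison of current side effects. That stands. A reader might infer that the scales cannot measure tolerability at all, but this would need months counted from the end of treatment, which the article does not say, and a recall period too short to reach back, which it does not give. For the same reason no percentage of treatment weeks covered can be stated.

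A reader might also infer that a FIBSER baseline is meaningless, or that off-treatment ratings will be near zero. The article supports neither. The edited items are not shown, participants may be taking several classes of psychotropic drug and continue usual care, and a pre-treatment rating is a sound reference, especially for a general inventory such as the PRISE. Late ratings can show persisting effects.

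Other parts of the reply stand too. Tolerability is not a named objective. Stopping rTMS is not the same as leaving the study, and those who stay are still contacted. Visit-specific contrasts may be set out in an analysis plan that is not shown. Interventions mentions standard program questionnaires of unstated content, and adverse-event recording may sit in the full protocol, so its absence here is no finding.

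None of this changes the timing of the two named outcomes. The patient experience questionnaire and focus group do not fill the gap, because Follow-up Assessment places them at 3 and 6 months.

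**Conclusion.** The point holds as one of sparse and possibly selective sampling. At most 1 of 4 ratings is on treatment under any of the three time origins, none is scheduled at the end of the course, and the later two fall 6.0 to 13.0 and 19.1 to 26.1 weeks after rTMS ends. These counts rest on the stated 6-week course and on baseline preceding the first session. The session counts also assume five sessions a week.

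Two consequences are conditional. Selection depends on how many participants leave before month 1, for which the article gives no figure, although Sample Size expects few to enroll and complete. Dilution depends on whether visits are averaged. The primary outcome is unaffected. This is a cheap improvement to two secondary scales on which the article predicts a difference between arms.

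**What to change.** 1. State the event from which the 1, 3 and 6 months are counted, and whether the 6-month observation includes the 6 weeks of treatment.
2. Add self-completed FIBSER and PRISE forms at fixed rTMS sessions, for example mid-course and session 30, or at the last session attended by anyone who stops early.
3. Keep the baseline ratings as the pre-treatment reference and the later ratings for persisting effects.
4. Specify the between-arm tolerability comparison at the fixed on-treatment time points. Do not use an average over all visits. A worst rating is also unsuitable, because it tends to rise with the number of forms completed and would count against an arm whose participants attend longer.

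This alters when the scales are completed and leaves treatment unchanged. No new visits are needed, since participants already attend for 30 sessions. The cost is a few minutes of added questionnaire burden during treatment.

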### Randomization and Blinding

A simple randomization technique will be used based on a single sequence of random assignments. A computer-generated Excel sheet (Microsoft Corp) will be used for simple randomization of subjects. Randomization will be stratified by using permuted blocks to ensure balance (1:1) between the two follow-up treatment groups. The randomization codes will be transmitted by an independent statistician via text message directly to a researcher’s password-protected phone line with a secure online backup. This will commence as soon as participants sign the consent forms.

As it will not be possible for participants to be blinded, treatment allocation will be made explicit to them as soon as randomization is concluded. Primary outcome assessors will be blinded to treatment group allocation by not involving them in discussions about study participants and not granting them access to the database that contains the randomization code. After data collection is complete, all data will undergo a blind review for the purposes of finalizing the planned analysis.

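### The randomisation code is released on the consent signature and the arm disclosed at once, while Table 1 puts baseline before randomisation: the order needs to be fixed in one sentence

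*Protocol article*

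**What the plan says.** The Randomization and Blinding section has an independent statistician send the codes by text message to a researcher, and then gives the timing: "This will commence as soon as participants sign the consent forms". The next paragraph adds that, because participants cannot be blinded, "treatment allocation will be made explicit to them as soon as randomization is concluded". That section names no other condition for releasing a code.

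Table 1 gives a different order. Its Milestone 2 line reads "2.1. Recruitment, baseline assessment, and randomization", followed by assignment to the arms.

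Eligibility is described in two places. The paragraph after the exclusion list says "Once the individual has been accepted into the rTMS program, a member of our research team will introduce the study to him/her", so acceptance into the rTMS programme comes before consent. Consent is then taken at a "face-to-face meeting with the eligible participant during the week of their rTMS eligibility assessment, which occurs 1 week before beginning the rTMS sessions". The Interventions section describes a visit one week before rTMS for motor threshold measurements and "and assessment for inclusion in the study", without saying whether this comes before or after the consent signature.

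The Outcomes section states: "The primary outcome measure will be the mean change in the scores on the Hamilton Depression Rating Scale". In Table 2 the HAM-D is clinician-rated, and it is assessed at baseline and at 1, 3 and 6 months.

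**The concern.** A baseline is safe to subtract, or to adjust for, because it is fixed before allocation. If the participant already knows the arm, disappointment or expectancy can colour the answers, and the measure becomes a post-randomisation variable. Adjusting for baseline would not repair this, because the covariate itself would carry an effect of allocation.

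Eligibility is the second issue. Acceptance into the rTMS programme is not the same as meeting the study's own criteria, which include a HAM-D of 10 or more, the Mini-International Neuropsychiatric Interview and a Montreal Cognitive Assessment threshold. If codes go out on the consent signature, a participant may be randomised, told the arm and then found ineligible. That forces a choice between excluding people after randomisation and keeping ineligible participants in the analysis.

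The trial also aims to supply effect sizes for planning a full trial, so a distorted contrast would be carried into that trial's sample size.

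**Working it through.** **Order of events.** No figure in the plan depends on this point. The sample of 100, about 50 per arm, is set by feasibility, so there is nothing to reproduce. The check is to set the statements side by side.

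| Place | What it fixes | What it leaves open |
|---|---|---|
| Randomization and Blinding | Code release follows the consent signature; arm disclosed at once | Any wait for inclusion checks or baseline |
| Table 1, Milestone 2 | Baseline listed before randomisation | Whether this is a rule or a label in a chart by quarter |
| Paragraph after Exclusion Criteria | rTMS programme eligibility settled before consent | Whether the study criteria are settled by then |
| Interventions | Inclusion assessment about one week before rTMS | Its order relative to consent |
| Randomization and Blinding | Primary outcome assessors blinded, no visit excepted | What the participant knows at baseline |
| Follow-up Assessment | Blinded researcher at 1, 3 and 6 months | Who rates the baseline |

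The first row is the only operating rule for code release, and it conflicts with the second. The other rows do not remove the conflict: none requires the baseline or the study criteria to be complete before the code goes out.

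**Which measures are exposed.** Five of the eight tools in Table 2 are self-rated (QIDS SR-16, FIBSER, PRISE, WHODAS 2.0, EQ-5D-5L). All five are secondary. The HAM-D is rated by a clinician, but it is scored from an interview with a participant who may know the arm.

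**How a shift carries through.** Let b be the between-arm difference in mean baseline HAM-D caused by knowledge of the arm, with follow-up scores unaffected. Change is follow-up minus baseline, so the between-arm difference in mean change moves by exactly b in size.

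**Illustration only.** Inputs:
- 50 per arm (Sample Size section).
- Two-sided 5% test and no true effect (assumed).
- SD of change of 7.0 (assumed). It is taken from the rTMS-versus-sham meta-analysis in the Introduction: 2.31 / 0.33 = 7.0. The article does not name the scale behind that figure, so SDs of 5 and 8 are also shown.

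SE = SD × √(2/50). For SD 7 this is 7 × 0.2 = 1.4.

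Rejection rate = Φ(b/SE − 1.96) + Φ(−b/SE − 1.96).

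For b = 1 and SD 7: Φ(0.714 − 1.96) + Φ(−0.714 − 1.96) = 0.106 + 0.004 = 0.110.

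| SD | b = 0.5 | b = 1 | b = 2 |
|---|---|---|---|
| 5 | 7.9% | 17.0% | 51.6% |
| 7 | 6.5% | 11.0% | 29.8% |
| 8 | 6.1% | 9.6% | 24.0% |

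The values of b are chosen for illustration. The documents give no basis for any of them.

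**The case against.** The strongest reply is that the article does give the right order, in Table 1, and that the sentence on timing may mean only that no code moves before consent. It does not say that baseline comes later. Programme eligibility is settled before consent, the consent meeting is with a person already called eligible, and a HAM-D is needed to establish the entry score. A condensed article also need not spell out every enrolment step.

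Much of this stands. A reader might infer that the plan prescribes a baseline taken after allocation; it does not. A reader might also infer that the baseline HAM-D is rated by someone who knows the arm. The documents do not support that either: primary outcome assessors are to be blinded with no visit excepted, and the follow-up section names a blinded researcher only at 1, 3 and 6 months because follow-up is its subject. A 1-point shift could be set against the 2.31-point difference quoted in the Introduction, but that difference is rTMS versus sham, not iCBT added to rTMS, so the ratio says nothing about this trial.

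Two things survive. The article does not merely omit the trigger; it states one, and the wording ties release directly to the signature. Assessor blinding does not govern what an informed participant says in an interview or enters on a self-rating form.

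**Conclusion.** The point holds as an inconsistency in a stated rule, with a real route to bias. The randomisation section allows allocation and disclosure before baseline and before the study criteria are confirmed; Table 1 implies the opposite; and the inclusion assessment is not ordered relative to consent. If staff follow the randomisation section literally and baseline has not yet been done, the primary change score loses its pre-allocation anchor, and exclusions after randomisation become possible.

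The mechanism is certain: any differential baseline shift enters the contrast one-for-one. Whether a shift would occur, and how large it would be, is unknown from the documents. The rejection rates shown rest on an assumed SD and chosen shifts, and no figure in the plan changes.

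**What to change.** Reconcile the Randomization and Blinding section with Table 1 by replacing the sentence on timing with:

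*The code is released only after consent is signed, all study eligibility criteria are confirmed, and all Table 2 baseline measures are completed and recorded.*

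This also settles where the inclusion assessment in the Interventions section belongs: before code release. No separate blinded baseline rater is needed, because a baseline recorded before the code exists for that participant is blind to allocation by construction.

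The cost is small but not nil. Consent, eligibility checks and baseline must all be finished before allocation, within the roughly one week before the first rTMS session. Because consent is taken during the week of the eligibility assessment, a full seven days is not assured, and the visit schedule should be checked against this.
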